### Participant timeline {13}

Potential participants are screened for study eligibility by telephone ± video link; consenting individuals undergo a remote (via video-link or, if not feasible, by telephone) baseline visit (day 1) within 24 h. Subsequent remote visits occur on days 7, 14, and 90; a single in-person visit is requested at day 35 to draw blood. The full schedule of events is shown in Table 1.

**Table 1 Tab1:** Schedule of events for the CORIPREV-LR trial

Visit	Screening (day 0)	Baseline (day 1)	Day 7, ± 2 days	Day 14, ± 2 days	Day 35, ± 4 days	Day 90, ± 2 days
**Visit format**	**Remote**	**Remote**	**Remote**	**Remote**	**In person**	**Remote**
Eligibility assessment	X					
Informed consent/assent	X					
Cluster randomization	X^a^					
Dispensation of study drug (LPV/r arm)		X				
Interview by study staff		X	X	X	X	X
Concomitant medication assessment		X	X	X	X	X
Adverse event assessment			X	X	X	X
Adherence diary (LPV/r arm)		Daily on d1–14				
Symptom diary		Daily on d2–15, then d21, d28, d35				
Temperature diary		Daily on d1–14				
Visit-specific questionnaire^b^		X		X	X	X
HIV self-test^c^		X				
Self-collected saliva sample		X	X	X	X	
Self-collected oropharyngeal/nasal swab^d^		X	X	X		
Self-collected dried blood spot		X^e^		X^f^		
Blood for SARS-CoV-2 serology		X^g^			X	
Stored blood samples					X	
Blood for CBC					X^f^	

^a^Randomization of the cluster occurs once all exposed contacts of an index COVID-19 case have provided their decision about study participation, or could not be contacted within 24 h of the study team becoming aware of the index case; once randomization has been completed then site coordinators should contact individual participants to conduct the baseline activities

^b^Specific components of each visit-specific questionnaire are listed in sections 13.3–13.7 below. Questionnaires can be completed on paper or via interview if internet access is unavailable. Guardians may complete questionnaires together with minors if preferred/not feasible by the minor

^c^ The HIV Self-test should only be done in participants over the age of 18 months; those under this age and those unable to perform the self-test for any reason (e.g., extreme needle phobia, limited manual dexterity) should undergo standard HIV testing at day 35 (HIV RNA test in those aged < 18 months; 4th generation antibody/antigen test for all others)

^d^An additional swab is to be collected within 24 h if symptoms develop before day 14. Two respiratory specimens (swabs, saliva, etc.) are to be taken at day 14 timepoint, unless an extra swab was already taken due to the development of symptoms in which case only one is collected

*NB:* other respiratory specimen(s) may be collected depending on availability of supplies

^e^The dried blood spot at baseline is to be performed in participants in the active arm only (since these participants are already collecting a drop of blood for the HIV self-test), for SARS-CoV-2 serology

^f^The dried blood spot at day 14 is to be performed in a random subsample of participants in the active arm only, for lopinavir levels. These participants are the only ones that require a CBC at day 35 since the hematocrit is required for interpretation of DBS lopinavir levels [42, 43]

^g^Baseline serology is to be collected at baseline only if the participant is institutionalized

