An initial clinical trial in China found no definite treatment benefit of LPV/r in hospitalized COVID-19 patients [9] but was underpowered for the primary endpoint of mortality, and initiation of LPV/r was late in the course of COVID-19 disease. There was also a potential for imbalance in baseline characteristics (higher viral load, later presentation, more severe illness in the LPV/r arm) to influence the outcomes. Secondary endpoints hinted at potential benefit (numerically lower mortality, shorter ICU/hospital stay) [9]. As noted by many observers [10–14], the results underscore the need for more LPV/r trials. While subsequent results from the SOLIDARITY and RECOVERY trials showed no impact of treatment with LPV/r on mortality in hospitalized COVID-19 patients [15, 16], data are lacking on the impact of this drug when used for prophylaxis or pre-emptive therapy.

The safety of LPV/r is already well-established, since it has been widely used in HIV treatment and PEP for over 20 years [17–19]. While it can cause temporary gastrointestinal side effects [20–23], discontinuation due to side effects was uncommon in HIV PEP trials [24–26]. Drug interactions are well understood [27], although the large number of potential interacting agents can pose clinical challenges. LPV/r is safe in pregnancy, liver disease and at all levels of renal function including dialysis and is available in liquid form to facilitate use in children and adults who cannot take pills/tablets [27]. It is also available worldwide, including in resource-limited settings. Thus, the feasibility of LPV/r as COVID-19 PEP is high if shown to be effective, and it is critical to develop evidence regarding its use.

This trial will examine the efficacy and safety of a 14-day course of LPV/r as PEP in close contacts of individuals with confirmed SARS-CoV-2 infection. All items in the WHO trial registry data set can be found in the protocol (Appendix A).

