### Strategies to improve adherence to interventions {11c}

Participants in the active arm of the trial will receive a few doses of dimenhydrinate 50 mg (for management of nausea) and loperamide 2 mg (for diarrhea) in their study kits, in order to help manage potential gastrointestinal side effects of the study drug.

Of note, the study team considered a loading dose of LPV/r at baseline (400/100 mg four times on day 1, followed by twice daily to complete 14 days total) in order to optimize the pharmacokinetics of this drug against SARS-CoV-2. However, this strategy was not selected due to concern that it may be associated with an increased risk of side effects that could compromise further adherence with the study drug.

Adherence will be monitored in two ways. First, participants in the active arm will be asked to complete a daily electronic symptom diary which asks whether each dose was early, on time (within 3 h), late, or forgotten/missed. Second, a random ~ 30% subset of participants in the active arm will have a self-collected dried blood spot collected at day 14 for testing of plasma lopinavir levels as a biomarker of adherence and to assess for a pharmacokinetic correlate of protection. Because these levels can be affected by hematocrit [42, 43], this subset of participants will also undergo a complete blood count at the day 35 in-person visit, together with the routine blood draw for serology.

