Adverse events: the proportion of participants exhibiting adverse events of any grade as defined using the DAIDS Table for Grading the Severity of Adverse Events, at 7, 14, 35, and 90 days [28].Symptomatic microbiologically confirmed SARS-CoV-2 infection: proportion of participants with fever, cough, or other respiratory/systemic symptoms (including but not limited to fatigue, myalgias, arthralgias, shortness of breath, sore throat, headache, chills, coryza, nausea, vomiting, diarrhea), combined with microbiologic confirmation of SARS-CoV-2 infection by PCR, by day 14.Seropositivity: proportion of participants with reactive serology at day 35.Days of hospitalization attributable to COVID-19 disease: The median number of days (or partial days) spent admitted to an acute care hospital will be tabulated both at day 35 and day 90.Respiratory failure requiring ventilatory support attributable to COVID-19 disease: The median number of days (or partial days) requiring (i) non-invasive or (ii) invasive ventilation will be tabulated both at day 35 and day 90.Mortality (proportion of participants who die) attributable to COVID-19 disease and all-cause mortality will be tabulated at 35 and 90 days.Short-term psychological impact of exposure to COVID-19 will be measured at day 14 using the K10, a validated measure of non-specific psychological distress, with results aggregated as the proportion with a score of ≥ 16 [45, 46].Long-term psychological impact of exposure to COVID-19 will be measured at day 90 using the Impact of Event Scale, a validated measure of traumatic stress response, with results aggregated as the proportion with a score of ≥ 26 [47, 48].Health-related quality of life will be measured using the EQ-5D-5L (EuroQol-5D) (https://euroqol.org/eq-5d-instruments/eq-5d-5l-about/). The EQ-5D consists of two pages: the EQ-5D descriptive system and the EQ visual analog scale (EQ VAS). The descriptive system comprises five dimensions: mobility, self-care, usual activities, pain/discomfort and anxiety/depression. The tool will be administered to participants at 1, 14, 35 and 90 days; the primary interest is in the median index value at 14 days.

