## Data collection and management

### Plans for assessment and collection of outcomes {18a}

At baseline, study staff will conduct interviews to capture baseline characteristics of the study sample, including demographics; exposure assessment (relationship with case patient; timing/intensity/frequency of contact; protective measures taken during contact); medical history (comorbidities, medications, smoking) and symptoms.

To obtain specimens for viral RNA testing (primary outcome), participants will be instructed on self-collection of oropharyngeal/nasal swabs as in prior work [64, 65], for RT-PCR testing [66–68]. Specifically, participants are asked to swab the back of their tongue, followed by the throat, before inserting the swab up to 4 cm into each nostril and rotating at least twice. These instructions are also provided in a short instructional video. Specimens will be collected at baseline, day 7, day 14 and within 24 h of new symptoms. In participants who are asymptomatic, a second self-collected swab will also be collected at day 14 and combined in the same specimen vial, or a saliva specimen will be collected if swabs are not available, since having two respiratory specimens tends to increase sensitivity for the detection of respiratory viruses [69, 70]. (If a participant has an earlier swab that is PCR positive then only one swab/saliva specimen needs to be collected at day 14.) Nasopharyngeal swabs and deep respiratory samples (e.g., bronchoalveolar lavage/endotracheal tube aspirates) already done for clinical care purposes will also be collected, with biobanking of specimens not tested in real-time for future analysis.

Follow-up interviews will be conducted at days 7, 14, 35, and 90 to assess for adverse events and clinical outcomes (hospitalizations, mechanical ventilation, mortality). Symptom data will be collected using daily electronic questionnaires that will be emailed daily for days 1–14. Participants will also be provided with a thermometer with which to record their temperature daily on days 1–14.

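### Two rules for the second day-14 respiratory specimen disagree, and under one of them a drug-related symptom can change how the primary outcome is ascertained

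*Protocol article*

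**What the plan says.** All references are to the protocol article.

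- **Primary outcome.** Outcomes {12} counts any PCR detection in a respiratory specimen by day 14. Specimens are taken at baseline, day 7, day 14 and after new symptoms, and saliva is an accepted specimen type.
- **Rule in the schedule.** Table 1 note d (Participant timeline {13}) begins: "An additional swab is to be collected within" 24 hours if symptoms develop before day 14. It then asks for two respiratory specimens at day 14, "unless an extra swab was already taken due to the development of symptoms in which case only one is collected". The result of the earlier swab plays no part.
- **Rule in the text.** Plans for assessment and collection of outcomes {18a} says: "In participants who are asymptomatic, a second self-collected swab will also be collected at day 14 and combined in the same specimen vial", with saliva as the fallback. The reason given is "since having two respiratory specimens tends to increase sensitivity for the detection of respiratory viruses". A parenthesis adds: "If a participant has an earlier swab that is PCR positive then only one swab/saliva specimen needs to be collected at day 14".
- **Drug effects.** Background and rationale {6a} says of lopinavir/ritonavir (LPV/r) that "it can cause temporary gastrointestinal side effects". Strategies to improve adherence {11c} supplies the active arm with medication for nausea and diarrhea "in order to help manage potential gastrointestinal side effects of the study drug".
- **Symptom list.** The symptomatic-infection outcome in Outcomes {12} includes "fatigue, myalgias, arthralgias, shortness of breath, sore throat, headache, chills, coryza, nausea, vomiting, diarrhea".
- **Blinding.** Who will be blinded {17a} describes an open-label trial and cites the objectivity of PCR in mitigation.

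**The concern.** Two things are at stake. First, sites have two instructions for the final sampling point of the primary endpoint, and the instructions do not always agree. Second, under note d the day-14 specimen count depends on something that happens after randomization and that the drug can bring about. Nausea or diarrhea in an LPV/r participant may prompt a swab. If it does, and the swab is negative, that participant gives one specimen at day 14 where most controls give two. The article itself says two are more sensitive. An objective assay protects an open-label comparison only if it is applied alike in both arms.

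**Working it through.** **1. The two rules side by side.** The {18a} column takes asymptomatic to mean asymptomatic at day 14.

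| Participant at day 14 | Note d | {18a} |
|---|---|---|
| Never symptomatic, no positive swab | two | two |
| Still symptomatic, earlier symptom swab negative | one | one (by implication) |
| Symptoms resolved, earlier symptom swab negative | one | two |
| Never symptomatic, day-7 swab positive | two | one |

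The fourth row is harmless, because that participant is already an event. The third is not: the participant is still at risk and the rules give different specimen counts.

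**2. The plan's own figure.** For 15% versus 9% (a 40% relative reduction), two-sided alpha 0.05 and 80% power, the normal approximation without continuity correction gives 460 per arm. The design effect is 1 + (5 − 1) × 0.05 = 1.2, so 460 × 1.2 = 552 per arm, or 552/5 = 110.4 clusters. The Abstract states 110 per arm, 220 in total. Then 220/0.9 = 244.4, and Sample size {14} states 244 rings, with 244 × 5 = 1220 participants. The plan is reproduced. Power at 110 clusters per arm is 79.9%. The specimen rule does not enter this calculation.

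**3. Inputs for the ascertainment check.** The article gives no PCR sensitivity and no gastrointestinal symptom rate. All of the following are assumptions, expressed per infected participant:

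- a, day-7 sensitivity: 0.4 or 0.6
- b and b2, day-14 sensitivity with one and two specimens: 0.70/0.80, 0.70/0.91 or 0.80/0.90
- c, yield of the symptom swab: 0 to 0.7
- f, share with a symptom swab, LPV/r versus control: 30% versus 5%, or 50% versus 10%

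**4. Day-14 component alone.** Sensitivity in an arm is f·b + (1 − f)·b2.

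- Largest gap (0.70/0.91, 50% versus 10%): (0.5 × 0.70 + 0.5 × 0.91) / (0.1 × 0.70 + 0.9 × 0.91) = 0.805/0.889 = 0.91.
- Smallest gap (0.80/0.90, 30% versus 5%): 0.870/0.895 = 0.97.

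The ratio is always below 1, meaning less sensitive in the LPV/r arm.

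**5. Cumulative outcome by day 14, which is the actual endpoint.** Without a symptom swab, detection is 1 − (1 − a)(1 − b2). With one it is 1 − (1 − a)(1 − b)(1 − c). Each arm is the average weighted by f.

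- Lowest ratio (a = 0.4, 0.70/0.91, c = 0, 50% versus 10%): the two paths give 0.946 and 0.820, so the arms are 0.883 and 0.933, ratio 0.946.
- Highest ratio (a = 0.4, 0.70/0.80, c = 0.7, 50% versus 10%): the paths give 0.880 and 0.946, so the arms are 0.913 and 0.887, ratio 1.030.
- Break-even: (1 − b)(1 − c) = 1 − b2. For 0.70/0.91 this is c = 0.7; for 0.80/0.90 it is c = 0.5.

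**6. Consequence for the test.** With an observed control risk of 15%, a true relative risk of 0.60 would appear as 0.57 to 0.62 (0.60 × 0.946 = 0.568; 0.60 × 1.030 = 0.618). Power would be 76% to 86% against 79.9%. Rejection under the null would be 5.0% to 6.4% against 5%.

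**The case against.** The strongest reply is that note d does not reduce testing; it moves one specimen earlier. A participant with one symptom swab has day 7, the symptom swab and one day-14 specimen; a participant without has day 7 and two at day 14. That is three post-baseline specimens either way, and all count. This stands, and it is why the sign of the net bias cannot be fixed. Equal counts are not equal sensitivity, though: a swab timed by drug intolerance may be worth more or less than a second day-14 specimen.

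Other replies narrow the point:

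- If asymptomatic in {18a} means never symptomatic, the third row of the table also agrees with note d. The text does not say which is meant, so the wording still needs settling.
- The article does not define which symptoms trigger a swab. The list with nausea, vomiting and diarrhea belongs to a secondary outcome. Nothing in the article excludes drug-type symptoms, but the trigger is an inference.
- Infection itself prompts symptom swabs in both arms, and an effective drug would reduce them in the LPV/r arm.
- Two swabs pooled in one vial are probably correlated. With 0.70 rising only to 0.75, and 40% versus 10% giving one specimen, the day-14 ratio is 0.730/0.745 = 0.98.
- Table 1 schedules saliva at day 14 for everyone. If it is routinely PCR-tested, the gap shrinks. {18a} says saliva will also serve antibody detection and leaves this unclear.

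A reader might infer that PCR sensitivity for the primary outcome is shown to be lower in the LPV/r arm, so that the trial is biased toward benefit. The article does not support that: the direction holds only for the day-14 component, and carrying it to the endpoint would give the symptom swab no yield. A reader might also infer that {18a} permits a single specimen only after a positive swab. It says if, not only if.

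**Conclusion.** The point holds as a textual conflict plus an ascertainment rule that can act differently in the two arms. The conflict affects participants with a negative symptom swab and resolved symptoms, who are still at risk of the primary outcome. Under note d, the number and timing of specimens depend on a post-randomization event that the drug can cause. Across the assumed inputs the cumulative detection ratio, LPV/r to control, runs from about 0.95 to 1.03: modest against a targeted 40% reduction, and of unknown sign. The range rests on sensitivities, symptom-swab yields and symptom-swab rates that the article does not give. The problem is worth correcting because it concerns the primary endpoint and costs little to remove.

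**What to change.** Replace note d's day-14 rule and the two sentences in {18a} with one rule for both arms: every participant without an earlier PCR-positive specimen gives two respiratory specimens at day 14, regardless of symptoms or earlier negative swabs. The second can be a swab in the same vial or the day-14 saliva already scheduled in Table 1. State which, and that it is PCR-tested alike in both arms.

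Also prespecify a sensitivity analysis of the primary outcome using only the scheduled day-7 and day-14 specimens. Neither part is enough alone:

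- With the rule but symptom swabs still counted, a = 0.4, b2 = 0.8, c = 0.5 and 50% versus 10% give 0.910 versus 0.886, a ratio of 1.03, because the LPV/r arm is then tested more.
- With the scheduled-only analysis but note d unchanged, the situation is c = 0 above, and the ratio is 0.946 to 0.990.
- With both, the number of scheduled specimens no longer depends on arm-related symptoms, and the day-14 sensitivity ratio is 1.00 by construction in the model above.

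The cost is one extra self-swab for some participants (pooled in the same vial, so no extra PCR run), a wording change, a site instruction and one extra analysis. The target of 244 rings does not change.

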### Sample size {14}

Our target sample size is 244 rings, assuming an average ring size of 5 individuals (i.e., a total of *n* = 1220 participants), an intra-class correlation coefficient (ICC) of 0.05 [31], a secondary attack rate (proportion of those exposed who get infected, p_0_) of 15%, and inflation for 10% loss-to-follow-up. This sample size will allow us to detect whether the study drug decreases the relative risk of COVID-19 by at least 40% (effect size estimated in the MERS-CoV LPV/r PEP study [8]), with 80% power and alpha = 0.05.

The number of contacts per case may vary considerably but was estimated at 5 based on published data for SARS in Beijing (mean = 3.8) [49]. We considered ICC values of 0.02 and 0.05 [31]. The estimated secondary attack rate of 15% was originally estimated based on transmission rates for SARS [49–52] and influenza [53–56] and is corroborated by recent studies on COVID-19. Among 19 household contacts of the first 10 patients with travel-related COVID-19 in the United States, *p*_0_ = 10.5% (95%CI = 2.9%–31.4%) [57]. In Shenzhen, the secondary attack rate among 686 household contacts was 11.2% (95%CI = 9.1–13.8) [58]. In Guangzhou, it was 19.3% (95%CI = 15.5–23.9%) among household contacts sharing a residential address with a case [59]. Investigators in Wuhan found secondary transmission in 64/392 household contacts (16.3%) [60]. Illness compatible with COVID-19 developed in 58/407 (14.8%) of placebo arm participants in a recent trial of hydroxychloroquine as COVID-19 PEP [61].

The parameters *p*_0_, ICC and cluster size are important drivers of statistical power [62, 63], but are still being elucidated for COVID-19 and may vary according to context. We will thus apply an adaptive trial design [63] to revise our sample size calculations based on day 14 data from the first 60 clusters.

Another interim analysis will be done when day 14 data for 50% of the target sample have accrued; our independent data safety monitoring committee will advise on trial continuation/switching to a different agent, taking external data into account, and through additional confidential consultation with the WHO Core DSMC on COVID-19 prophylaxis, with which we are linked [5].

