## Statistical methods

### Statistical methods for primary and secondary outcomes {20a}

The primary outcome is microbiologically confirmed SARS-CoV-2 infection, i.e., detection of viral RNA in a respiratory specimen (oropharyngeal/nasal swab, nasopharyngeal swab, sputum specimen, saliva specimen, oral swab, endotracheal aspirate, bronchoalveolar lavage specimen) by day 14. Our primary analysis will be a generalized linear mixed model (GLMM) with logit link to estimate the effect of LPV/r on the probability of infection while accounting for clustering of participants in rings, with stratification by the randomizing site. The primary analysis will be unadjusted; in addition, multivariable models will adjust for key characteristics of both contacts (age, sex, co-morbidity, exposure characteristics such as type, duration, and timing) and index cases (illness severity, concomitant medications, etc.). In particular, we will include sex/gender-based analyses with variables specific to contacts and types of exposures. Participants with specimens positive for SARS-CoV-2 at baseline will be permitted to continue in the trial and follow all study procedures, including completion of the 14-day course of study drug for those in the active arm, as noted in section 12.2.2. These participants will be excluded from the primary and secondary analyses regarding LPV/r as PEP, but included in secondary analyses regarding early LPV/r treatment, as noted below.

To assess safety, adverse events will be tabulated according to grade and causality assessment using definitions from the DAIDS Table for Grading the Severity of Adverse Events [28], and compared between study arms.

As for the primary analysis outlined above, GLMM with logit link (for dichotomous outcomes) or identity link (for continuous outcomes) will also be used to compare the following secondary outcomes between study arms:

Symptomatic COVID-19 disease by day 14Seropositivity by day 35Days of hospitalization attributable to COVID-19 disease by day 90Respiratory failure attributable to COVID-19 disease requiring (i) non-invasive and (ii) invasive ventilation by day 90Mortality attributable to COVID-19 diseaseShort-term psychological distress, defined as scoring ≥ 16 on the K10 [45, 46] at day 14Long-term traumatic stress response, defined as scoring ≥ 26 on the IES scale [47, 48] at day 90Health-related quality of life, measured by the EQ-5D-5 L on days 1, 14, 35, and 90

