To date, several clinical trials of COVID-19 PEP have already been completed and reported. An initial team of American and Canadian investigators randomized 821 asymptomatic adults who reported a household or occupational exposure to someone with COVID-19 within the preceding 4 days, to receive either hydroxychloroquine or placebo, and noted no statistically significant difference in the incidence or either laboratory-confirmed COVID-19 or a compatible illness over the subsequent 14 days [61]. A shortcoming of this trial was that the availability of microbiologic testing for outcome ascertainment was limited, such that infection was confirmed by polymerase chain reaction in only 14% of participants with symptomatic disease. Our trial will overcome this limitation by using specimen self-collection, and testing of these samples within 24 h for SARS-CoV-2. Two subsequent trials of hydroxychloroquine as COVID-19 PEP have similarly shown no impact of that drug on acquisition of SARS-CoV-2 infection, using microbiologically confirmed infection by PCR as the primary outcome [78, 79].

Another novel feature of our trial design is our inclusion of baseline testing for COVID-19 in all participants. This approach will further allow us to explore the impact of lopinavir/ritonavir in the early treatment of COVID-19, since those who test positive at baseline will continue all study activities. Despite high-quality trials demonstrating that lopinavir/ritonavir is not effective as treatment in hospitalized COVID-19 patients, questions about its efficacy in early-stage treatment and prophylaxis remain unanswered. Only one other clinical trial is examining the efficacy of lopinavir/ritonavir as COVID-19 PEP, using an individual-randomized design [80].

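### The 80% power is calculated for all exposed contacts, but the primary analysis excludes those already PCR-positive at baseline, and nothing in the sample size allows for this

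*Protocol article*

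**What the plan says.** Sample size {14} sets a target of 244 rings, "assuming an average ring size of 5 individuals", 1220 people in all. It uses an ICC of 0.05, p0 = 15% and an allowance for 10% loss to follow-up. It defines p0 as the "secondary attack rate (proportion of those exposed who get infected". It then claims: "This sample size will allow us to detect whether the study drug decreases the relative risk of COVID-19 by at least 40"%, "with 80% power and alpha" 0.05. The Abstract gives 110 rings per arm before the allowance for loss.

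Statistical methods {20a} says of participants whose baseline specimens are positive: "These participants will be excluded from the primary and secondary analyses regarding LPV/r as PEP". The Abstract and Eligibility criteria {10} say the same for the primary analysis. Eligibility criteria {10} admits contacts exposed 1 to 7 days earlier. The primary outcome is PCR positivity by day 14.

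Sample size {14} also commits to revising the calculation from day 14 data on the first 60 clusters, because p0, ICC and cluster size are uncertain. It does not say in which participants they will be computed. Interim analyses {21b} gives 122 clusters as half of the revised target, which is again 244.

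**The concern.** The rate that drives the calculation and the set that will be analysed are defined on different populations. A contact infected by the index case and already shedding on day 1 counts towards the 15% as defined, but is removed from the primary analysis. Removal lowers the number analysed slightly and the control event rate more. Entry is allowed up to a week after exposure, and the article plans an early-treatment analysis in baseline-positives, so the plan itself foresees such participants. The sample size makes no allowance for them.

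The stated power, and the claim that a 40% reduction is detectable, would then not describe the primary analysis. A re-estimation that used p0 as defined would carry the mismatch into the revised target.

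**Working it through.** **Inputs from the article.** p0 = 15%; relative reduction 40%, so 9% under treatment; alpha 0.05 (two-sided reproduces the figure); ICC 0.05; ring size 5; 10% loss; 244 rings, or 122 per arm.

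**Input not in the article.** f is the share of secondary infections already PCR-positive at baseline. It is an assumption, shown from 0 to 0.5. As a share of all enrolled it is b = 0.15f.

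**Step 1: the plan's own figure.**
- n per arm = (1.96 + 0.8416)² × (0.15×0.85 + 0.09×0.91) / 0.06² = 456.5.
- Design effect = 1 + (5 − 1)×0.05 = 1.20.
- Rings per arm = 456.5 × 1.20 / 5 = 109.6, so 110, as stated.
- 220 / 0.9 = 244 rings, and 244 × 5 = 1220, as stated.

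**Step 2: power at the target after loss.** Ring size after loss is 5 × 0.9 = 4.5, so 122 × 4.5 = 549 per arm. Design effect = 1 + 3.5×0.05 = 1.175, and effective n = 549 / 1.175 = 467.2. SE = √[(0.1275 + 0.0819) / 467.2] = 0.0212. Power = Φ(0.06/0.0212 − 1.96) = 81%.

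**Step 3: exclude baseline-positives.** The 40% reduction is assumed to apply to infections appearing after baseline.
- Control rate: p0′ = 0.15(1 − f) / (1 − 0.15f)
- Ring size: m = 4.5(1 − 0.15f); n = 122m per arm
- Design effect: 1 + (m − 1)×0.05
- Power = Φ(0.4p0′/SE − 1.96), SE from p0′ and 0.6p0′ at the effective n

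Example, f = 0.2: p0′ = 0.12/0.97 = 12.4%; m = 4.365; n = 532.5; design effect 1.168; effective n = 455.8; SE = 0.0197; power = Φ(0.0495/0.0197 − 1.96) = 71%.

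| f | Positive at baseline, of all enrolled | p0′ | Power for 40% reduction | Reduction detectable at 80% power |
|---|---|---|---|---|
| 0 | 0% | 15.0% | 81% | 40% |
| 0.1 | 1.5% | 13.7% | 76% | 42% |
| 0.2 | 3.0% | 12.4% | 71% | 44% |
| 0.33 | 5.0% | 10.6% | 63% | 48% |
| 0.5 | 7.5% | 8.1% | 50% | 55% |

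The last column solves the same formula for the reduction that gives 80%.

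**Step 4: the alternative reading.** If 15% already means the rate among baseline-negatives, only numbers are lost. With 15% versus 9% and the reduced n, power is 80%, 80%, 79% and 78% at f = 0.1, 0.2, 0.33 and 0.5.

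**Step 5: other planning values.** The same formula with an attack rate of 19.3%, the highest COVID-19 rate cited in Sample size {14}, gives 83% at f = 0.2 and 80% at f = 0.25. With ICC 0.02, which that section also considered, and 15%, it gives 80% at f = 0.1. At 11.2%, another cited rate, it gives 67% at f = 0 and 57% at f = 0.2.

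**The case against.** The strongest reply is that p0 was meant as an incident rate. Objectives {7} and Statistical methods {20a} gloss it as an incidence proportion, and Outcomes {12} describes the primary outcome as incident infection. On that reading the loss is small (step 4). But both glosses apply the term to exposed contacts, not to baseline-negatives, and the only definition in Sample size {14} covers those exposed. The wording is not decisive enough to rescue the stated figure, though it makes the intended meaning uncertain.

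The second reply is that the 80% is provisional, since the target is to be revised after 60 clusters. This stands as a real safeguard. Day 14 data are primary-outcome data, so the re-estimation may well be run in baseline-negatives. The article does not say so.

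The third reply is that the size of the loss rests on f, which no document gives. That stands too. The stated 6.4-day incubation period is not a time to PCR positivity, and 7 days is the entry limit, not the typical delay. Step 5 shows that other cited planning values move power both ways.

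A reader might go further and argue that a ring size of 5 is too high because the cited mean is 3.8, that the hydroxychloroquine trial's rate cannot support p0, or that the household rates count every secondary case. These are not part of this point. The ring size and its basis are disclosed, and it is to be re-estimated. The article attributes the low PCR confirmation in that trial to limited testing. It does not report how the household studies counted cases.

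**Conclusion.** The point holds as a mismatch between the population in the power statement and the population in the primary analysis. Under the printed definition of p0, the 80% stated for 244 rings does not belong to the analysed set. The arithmetic itself is correct for all exposed contacts. With a reserve of about one percentage point, f = 0.1 (1.5% of enrolled positive at baseline) already takes power to 76%, and the range reaches 50% at f = 0.5. These values assume a 15% overall attack rate, a 40% reduction in post-baseline infections, ICC 0.05, 122 rings per arm and 10% loss.

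A reader might infer that the trial is underpowered. The documents do not support that. The baseline-positive share is unknown, a higher attack rate or lower ICC could offset a modest share, and the re-estimation could restore power if done in baseline-negatives. What is shown is that the stated power makes no allowance for the exclusion, and that the planned repair is not tied to the right population.

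**What to change.** Three text changes:

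1. In Sample size {14}, define p0 as incident PCR positivity by day 14 among participants who are PCR-negative at baseline.
2. Restate the power, or the detectable relative reduction, for that set over a short range of baseline-positive shares, as in the table above.
3. State that the 60-cluster re-estimation computes p0, ICC and ring size in baseline-negative participants with an evaluable outcome.

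No added enrolment is requested. The cost is a less favourable stated power. If 15% was always meant as the rate among baseline-negatives, saying so and giving its basis limits the change to about 78–80% over the range shown.
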